## Abstract

**Background:**

Guidelines in pediatric restorative dentistry recommend the use of preformed pediatric stainless steel crowns (SSCs) in cases of severe tooth decay of at least two surfaces. This clinically effective and safe restorative option is frequently refused by parents for esthetic reasons; they prefer conventional restorations using esthetic filling materials (composites, glass ionomer) if lesion severity limited to two surfaces permits. Recently, manufacturers have proposed esthetic preformed pediatric zirconia crowns (ZCs) but these have been assessed in only two randomized clinical trials (RCT) with follow-ups of 6 and 12 months. Only one of these RCTs was carried out on primary molars to test ZCs (NuSmile ZR) without a groove in its inner surface. The primary objective of this proposed RCT is to assess the effectiveness of ZCs compared with SSCs. Our hypothesis is that the effectiveness of ZCs will be equivalent to that of SSCs.

**Methods:**

In this split-mouth, 2-year RCT, pairs of primary molars in 101 child participants will be randomized and restored with SSCs (ESPE, 3M) and ZCs (EZCrowns, Sprig Oral Health Technologies) characterized by grooves on their inner surface. Primary molars will first be allocated to SSCs, and 1 to 2 weeks later the other primary molar of the same pair will be restored by ZC. The primary outcome is the success defined by the “absence of major clinical and radiographic failure” (e.g., pain, pulp infection, dental abscess or periradicular pathology visible on radiographs). The secondary outcomes include the retention and fracture rates, the gingival condition, the wear of the antagonist of the treated teeth, as well as both parental and child satisfaction.

**Discussion:**

This study will investigate two types of preformed pediatric crowns for the management of severe decay on primary molars. The results may help practitioners choose the better therapeutic option and to explain to parents the advantages and disadvantages of these two therapies.

**Trial registration:**

NCT03296709. Registered on  27 September 2017.

**Electronic supplementary material:**

The online version of this article (10.1186/s13063-019-3559-1) contains supplementary material, which is available to authorized users.

## Background

For many years, the preformed pediatric metal crown (stainless steel crown (SSC)) was considered, without established scientific evidence, the best method of restoring primary molars (PMs) affected by severe carious lesions because of its higher longevity than conventional restorations using various filling materials (amalgams, composites, glass ionomer) [1]. In 2008, SSCs were recommended by the British Society of Pediatric Dentistry [2]. In 2015, a systematic review assessed the effectiveness and the safety of the various types of preformed pediatric crowns (PPCs) compared with various types of filling material (amalgam, composite, glass ionomer). This systematic review evidenced the effectiveness of SSCs and the authors considered them the most appropriate restorative technique when compared with traditional methods (relative risk = 0.18; 95% confidence interval (CI) 0.06–0.56) over a 12- to 24-month period [3]. In this systematic review, effectiveness was defined as the absence of “major failure,” defined as a composite measure of signs and symptoms leading to diagnosis of irreversible pulpitis or periradicular periodontitis (pain, pulp infection, dental abscess, periradicular pathology visible on radiographs). Henceforth, SSCs were proposed as the sole technique for coronal restorations by one of the few associations who propose good practice recommendations taking into account the evidence base—the American Association of Pediatric Dentistry—when carious lesions or structural anomalies affect more than two surfaces of the PMs. SSCs are one of the techniques recommended for coronal restorations if two surfaces are involved [4]. Unfortunately, SSCs are frequently refused by parents for esthetic reasons [5]. Recently, some manufacturers—Hass Corporation (Gangwon-do, Korea), Kinder Krowns (St Louis Park, MN, USA), NuSmile (Houston, TX, USA), and Sprig Oral Health Technologies (Loomis, CA, USA)—have proposed esthetic PPCs called zirconia crowns (ZCs).

Another systematic review [6] published in 2016 having the primary objective of comparing the effectiveness of PPCs by including at least one group of esthetic crowns did not identify any randomized clinical trial (RCT) that compared ZCs with one of the other categories of PPCs on the PMs.

Since 2016, only two RCTs were identified on https://clinicaltrials.gov and http://apps.who.int/trialsearch/Default.aspx; one published [7] and the other not yet completed. The published RCT (NCT03067337, first submitted 22 January 2017) assessed the effectiveness of ZCs (NuSmile) compared with SCCs. This RCT reported that the effectiveness of ZCs was similar to that of SCCs in terms of cracks, chips, and fractures. However, gingival and plaque indices were lower among ZCs than SCCs. Even if this RCT suggests that ZCs are better than SCCs, caution is necessary in interpreting the results. First, the power of the analysis comparing cracks, chips, and fractures between ZCs with SCCs may be lower since the author justified the sample size based only on the gingival index. Second, it was also unclear how many teeth per participant were included since the authors reported that a sample of 120 contralateral molars in 26 patients had been treated [7]. The incomplete RCT (NCT01919515) comparing ZCs (NuSmile ZR) with SSCs in PMs is noted to be without recruitment since 2014.

ZCs manufactured by NuSmile differ from other ZCs by having no grooves on their inner surface. In order to improve retention and to absorb stresses in ZCs, other manufacturers (Kinder Krowns, Sprig Oral Health Technologies) have integrated grooves in the inner occlusal and axial surfaces of the PPCs (Fig. 1). Theses grooves are wider in EZCrowns (Sprig Oral Health Technologies). No RCT has so far evaluated these particular ZCs characterized by large inner surface grooves (EZCrowns). Thus, a split-mouth RCT comparing the effectiveness of ZCs (EZCrowns) and SSCs, considered as the reference PPC for PMs [2–4], must be carried out.

**Fig. 1 Fig1:**
[figure not shown]
Characteristics of different zirconia crowns (ZCs)

## Objectives and hypotheses

The overall aim of this RCT is to investigate the effectiveness of a new esthetic therapeutic option (EZCrowns; Sprig Oral Health Technologies) for the management of dental caries or structural anomalies. More specifically, the primary objective of this RCT is to assess the success of ZCs in PMs in comparison with SSCs with a follow-up of 2 years. The control treatment will be SSCs since this is the standard crown option [2–4].

Due to the esthetic superiority of ZCs (being a natural dental color) in comparison with SSCs (being metallic), our working hypothesis is that the success rates are equivalent between the ZCs and SSCs, given the absence of any major failure defined by Innes et al. [3] as a composite criterion including clinical and radiographic criteria.

The secondary objectives are to evaluate the retention and fracture rates, the gingival condition (plaque index, gingival index and depth of the pocket of Löe and Silness [8]), the wear of antagonist teeth [9, 10], and parental and child satisfaction (using a Likert scale) [11] between the study groups during the same period.

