### Sample size

Table 2 shows the sample size calculation for success rates ranging from 95% to 97%, alpha equal to 5%, with 90% power and an equivalence margin between the study groups of 10%. This table illustrates that the effective sample size of 81 teeth per treatment group will provide a power of 90% to assess effectiveness equivalence between the treatment groups. These rates were based on the systematic review of Innes et al. [3]. This calculation was based on the formula (Z _0.95_ + Z _0.90_)^2^ [Ps (1 – Ps) + Pn (1 – Pn)] / (Ps – Pn – D)^2^ (see http://people.ucalgary.ca/~patten/blackwelder.html) [14].

**Table 2 Tab2:** Sample size calculation

Rate	Teeth	Total required
80	274	548
85	218	438
90	154	308
95	81	162
97	49	98

Note: Rate of the outcome for the study groups, power = 90%, alpha = 5%, equivalence margin = 10%

Additionally, when we consider a hazard ratio (HR) = 1, moderate intraclass correlation (ICC) = 0.05, the percentage of teeth in each study group of 50%, the probability of observing an event of 90%, and two one-sided test (TOST) Zα = 1.64, this sample size of 81 teeth provides 80% power to test the equivalence between the study groups for margins ranging from 0.7 to 0.9. This sample size was calculated as described in [15].

Furthermore, assuming a dropout around 20%, the total sample size necessary will be 101 children. This dropout value was based on the experience of the research team from previous RCTs conducted in France [16]. This sample size is higher than those of past RCTs assessing the effectiveness of esthetic PPCs, which included 11 to 60 teeth per treatment group [6, 7].

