## Discussion

At present, the success and reliability of SSCs is known [3]. Even if SCCs are recommended in the treatment of severe tooth decay in children, few dental practitioners adopt their use in clinical practice; one of the reasons for this is their poor esthetic appearance [5]. An esthetic alternative to SSCs is ZCs. They would be more widely adopted by both clinicians and policy makers if the evidence showed that their success rate is equivalent to the success rate of SCCs. ZCs are supported by only a few valid studies evaluating their effectiveness and reliability [7]. To date, only a few case series focusing on restoration of PMs with ZCs have been published; these concluded that they perform well [18–23]. There are no prospective clinical trials using a search of PubMed on the performance of ZCs on PM. Only one RCT with a high risk of bias has been carried out in 26 children with a follow-up of 12 months [7]. The establishment of a suitably powered clinical trial comparing SSCs and ZCs is essential, and an evaluation of the long-term success of ZCs compared with SCCs is required. This trial may help address this issue as it involves nine centers nationwide and the possible recruitment of a large sample of 101 patients. In addition, the inclusion criteria are broad and thus there is variation in the patients included, especially in terms of the individual risk of caries. Hence, the external validity of the data should be optimized.

All current recommendations from the Standard Protocol Item Recommendations for Interventional Trials (SPIRIT) statement were taken into account in the design of the present clinical trial figure [24] (see Additional file 1). In terms of internal validity, the sources of bias are limited by the use of centralized randomization (selection bias) and strict prospective data recording and monitoring (information bias). However, because of the color of the PPCs, the operators, patients, and evaluators cannot be blinded. We selected the split-mouth design for this RCT because it enabled us to control for potential confounders that could distort the results.

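### The primary question is framed as two-sided equivalence, but the rationale and the sample-size formula are those of non-inferiority, and 81 pairs give about 80%, not 90%, power for equivalence at 95% success

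*Protocol article*

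**What the plan says.** The Abstract states "Our hypothesis is that the effectiveness of ZCs will be equivalent to that of SSCs". The Objectives and hypotheses section repeats it: "our working hypothesis is that the success rates are equivalent between the ZCs and SSCs, given the absence of any major failure". The reason given in the same sentence is "Due to the esthetic superiority of ZCs (being a natural dental color) in comparison with SSCs (being metallic"), and that section names SSC as the control because it is the standard option. The Discussion gives the intended use of the result: "They would be more widely adopted by both clinicians and policy makers if the evidence showed that their success rate is equivalent".

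The Sample size section plans on "success rates ranging from 95% to 97" per cent, with "alpha equal to 5%, with 90% power and an equivalence margin between the study groups of 10" per cent. It arrives at 81 teeth per group by a formula with one bound, D, and the quantiles z(0.95) and z(0.90), and presents this as 90% power for equivalence. A second calculation in that section names two one-sided tests (TOST) on the hazard ratio (HR), with margins from 0.7 to 0.9. The Statistical analysis section plans to assess equivalence with a shared-frailty Cox model that reports an HR and its 95% confidence interval.

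**The concern.** If ZC is already preferred for its colour, the evidence needed for adoption is that it does not fail more often than SSC. Fewer major failures with ZC would strengthen that case, and the protocol gives no reason to rule such a result out. Equivalence nevertheless requires ruling it out, to within the margin.

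Two things are at stake. First, the 90% power attached to the equivalence claim belongs to one bound only. Second, a trial in which ZC does as well as SSC or better could be reported as equivalence not shown, solely because the limit on the favourable side was crossed. The better ZC truly is, the more often that happens.

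**Working it through.** **Inputs.** From the Sample size section: success 95% to 97% in both groups, margin 0.10, alpha 5%, 81 per group, 20% dropout. Assumed: within-pair correlation of success 0. The protocol gives an intraclass correlation (0.05) only for its HR calculation, so 0.05 and 0.2 were also tried.

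**The plan's own figure.** n = (1.645 + 1.282)² × [2 × 0.95 × 0.05] / 0.10² = 8.564 × 0.095 / 0.01 = 81.4, against 81 in Table 2. The 97% row gives 49.8 against 49. Dropout: 81 / 0.8 = 101.25, against 101. The table is therefore reproduced by a one-sided 5% calculation with a single bound, apart from rounding down.

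**Power of 81 for one bound and for two.** At 95% in both groups, SE = √(2 × 0.95 × 0.05 / 81) = 0.0342, and 0.10 / 0.0342 − 1.645 = 1.275. One bound is met with probability Φ(1.275) = 0.899; both with 2 × 0.899 − 1 = 0.798. For 90% power on both bounds at equal rates, n = (1.645 + 1.645)² × 0.095 / 0.01 = 102.8, that is 103 per group, or 103 / 0.8 = 129 children.

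**Exact check.** All outcomes of 81 pairs were enumerated at correlation 0, using Wald limits for the paired difference ZC minus SSC at one-sided 5% per bound:

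| True SSC / ZC success | Lower bound met | Both met | Fails on upper only |
|---|---|---|---|
| 95 / 95 | 89.8% | 79.6% | 10.2% |
| 95 / 97 | 98.7% | 81.6% | 17.1% |
| 95 / 99 | >99.9% | 71.7% | 28.3% |
| 95 / 100 | 100% | 61.9% | 38.1% |
| 97 / 97 | 97.2% | 94.5% | 2.8% |
| 97 / 99 | >99.9% | 93.9% | 6.1% |
| 97 / 100 | 100% | 90.3% | 9.7% |

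At 95 / 95, correlation 0.05 gives 91.0% and 82.0%; correlation 0.2 gives 94.2% and 88.3%. At 95 / 100 correlation makes no difference.

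**A concrete case.** With no ZC failures in 81 pairs, four SSC failures give an upper limit of 0.0494 + 1.645 × 0.0241 = 0.089, a pass. Five give 0.0617 + 1.645 × 0.0267 = 0.106, a fail. A flawless ZC result would then miss equivalence.

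**What the upper bound means on each scale.** On the proportion scale, the largest possible true ZC advantage is 100 − 95 = 5 points, or 100 − 97 = 3 points. Whenever SSC success exceeds 90%, a true advantage of 10 points cannot occur, so showing that ZC is not worse by 10 points already places the true difference within ±10. On the HR scale the favourable bound can be reached. Under proportional hazards, ZC success = SSC success^HR, so against SSC at 95% the margins 0.7 and 0.9 correspond to ZC success of 0.95^0.7 = 96.5% and 0.95^0.9 = 95.5%. A ZC at 98% has HR = ln 0.98 / ln 0.95 = 0.39, outside every stated margin.

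**The case against.** Equivalence is a permissible aim and the protocol words it consistently; non-inferiority is never mentioned. The Abstract's discussion also speaks of helping practitioners choose between the two crowns, which has two directions. This stands: the one-sided rationale is inferred from the reasons given, so the point is a poorly fitted design choice and not a contradiction in the stated hypothesis. The mismatch between the one-bound formula and the equivalence power claim needs no such inference.

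A reader might infer that the protocol commits itself to a verdict of ±10 points on the risk difference. It does not. The 10-point margin appears only in the sample-size calculation, and the planned analysis is a Cox HR. The figures above therefore show what the sample-size premises imply; they do not describe the planned model.

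A reader might also infer that the favourable bound guards against an impossible result and so carries no information. That holds only for proportions with SSC above 90%. On the HR scale the bound is reachable and does carry information. There the difficulty is a different one: a clearly better ZC lies outside the margin by definition.

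Larger losses arise if SSC success is put at 92% or 93%, but those rates lie outside the planned 95% to 97%, and at 97% in both groups the loss is under 3 points. Finally, a careful reader of the interval would often see the truth: at 95 / 97, about two-thirds of the upper-only failures (11.4 of 17.1 points) have a lower limit above zero. That softens the harm, but the formal conclusion would still be that equivalence was not shown.

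**Conclusion.** The concern holds in this form. The rationale and the sample-size formula both belong to a non-inferiority question, while the hypothesis and the power claim are stated as equivalence. At 95% success, the rate that sets n = 81, power for equivalence is about 80% against the stated 90%; at 97% it is about 94%. The chance of failing on the favourable side alone is 10% to 38% at SSC 95% as ZC goes from 95% to 100%, and about 3% to 6% at SSC 97% for ZC from 97% to 99%.

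These figures assume a 10-point margin on the paired difference, one-sided 5% per bound, 81 evaluable pairs and correlation 0. Positive correlation reduces the loss when the rates are equal, and hardly does so when ZC is close to 100%. The design remains usable; what needs changing is the hypothesis and the rule by which the result is judged.

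**What to change.** By amendment before analysis, and without sight of outcomes by group:

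- Restate the primary hypothesis as non-inferiority of ZC to SSC in 24-month success, consistently in the Abstract, Objectives and hypotheses, Sample size, Statistical analysis and Discussion.
- Base the verdict on the lower one-sided 95% limit of the paired difference, ZC minus SSC, against −10 points. Report the two-sided interval descriptively.
- Keep the Cox HR as a supporting analysis, without a TOST verdict.

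The 81 teeth and 90% power at 95% success are then correct as they stand, at the one-sided 5% already in the formula, with no added children, visits or data. A stricter one-sided 2.5% would need 100 per group, or 100 / 0.8 = 125 children.

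If equivalence is kept, state its power at 95% success as about 80%; 90% would need 103 per group, or 129 children.

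The cost is that the conclusion reads non-inferior and not equivalent, and that the favourable side is no longer formally tested. On the proportion scale this loses nothing while SSC success is at least 90%. Because recruitment has begun and evaluators are unblinded, the reason for the change should be documented. It needs the steps listed under Ethical consideration: scientific board, ethics committee, national agency and trial registry.

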## Methods

### Trial design and blindness

In this multicenter split-mouth RCT, a PM and its contralateral tooth in the same arch will be randomly assigned to a specific crown treatment group, ZC or SSC (Fig. 2). We plan to screen 101 individuals to successfully recruit 81 patients (see Sample size section below). We decided to use the split-mouth design because each subject forms its own control, adjusting for potential confounders.

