### Recruitment procedures

Participants will be recruited in nine Departments of Pediatric Dentistry in the university hospitals of Bordeaux, Lille, Nancy, Nantes, Nice, Paris Bretonneaux, Paris Louis Morrier, Strasbourg, and Toulouse. Each center will recruit an average of 12 children (inclusion from September 2018 to February 2020). The participant's timetable is shown in Fig. 2 and the flow chart of the study is shown in Fig. 3. To encourage recruitment in order to reach the target sample size in the 18-month period, the principal investigator ([name]) will send a text message of encouragement, with general center recruitments mentioned after each inclusion.

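### The design section states the enrolment target as 81 recruited from 101 screened, whereas the sample-size section needs 101 enrolled to keep about 81 pairs after dropout

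*Protocol article*

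**What the plan says.** The protocol article gives the enrolment target in several places.

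- **Trial design and blindness:** "We plan to screen 101 individuals to successfully recruit 81 patients (see Sample size section below". Here 101 is the number screened and 81 the number recruited, and the reader is referred to the Sample size section.
- **Sample size:** "the effective sample size of 81 teeth per treatment group will provide a power of 90" (percent). In this split-mouth design, 81 teeth per group means 81 children with one pair each. The section then adds: "assuming a dropout around 20%, the total sample size necessary will be 101 children". On the source of the 20% it says: "This dropout value was based on the experience of the research team from previous RCTs conducted in France".
- **Abstract, Methods:** "pairs of primary molars in 101 child participants will be randomized".
- **Recruitment procedures:** nine centres are listed, and "Each center will recruit an average of 12 children".
- **Discussion:** the sample that may be recruited is put at 101 patients.

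**The concern.** The same two numbers carry different labels. In the Sample size section, 101 is the count before attrition and 81 the count after it. In the design section, 101 is the count before eligibility screening and 81 the count entering the trial.

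These are different stages. Under Recruitment procedures, a child is included only after the eligibility check and signed consent. Under Randomization, allocation follows inclusion. A recruited child has therefore already passed screening, and dropout can only come later, during the two years of follow-up.

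Read as written, the design sentence uses up the 20% allowance before follow-up begins and leaves nothing for attrition. A team that took 81 as its recruitment target would finish with fewer pairs than the calculation requires. The Possible problems section already names sample size as a difficulty because suitable pairs may be hard to find, so a sentence that appears to permit the lower figure should not stand.

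**Working it through.** **Inputs (all from the Sample size section unless noted).** Success rate 95% in both groups, the row of Table 2 that gives 81, with 97% as the upper end of the planned range; margin D = 0.10; quantiles Z0.95 = 1.645 and Z0.90 = 1.282; dropout 20%; nine centres averaging 12 children (Recruitment procedures).

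**Step 1: reproduce the 81.** With equal rates the plan's formula is n = (Z0.95 + Z0.90)² × 2P(1 − P) / D².
- At P = 0.95: 8.564 × 0.095 / 0.01 = 81.36. The plan states 81.
- The other rows of Table 2 (80%, 85%, 90%, 97%) come to 274.0, 218.4, 154.1 and 49.8, against 274, 218, 154 and 49. The table reproduces, apart from rounding down.

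**Step 2: reproduce the 101.**
- 81 / (1 − 0.20) = 101.25. The plan states 101.
- The alternative 81 × 1.20 = 97.2 does not give 101.
- In reverse, 101 × 0.80 = 80.8, about 81 pairs.

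So 101 is the number enrolled and 81 the number left after dropout.

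**Step 3: see which target the other sections support.**
- The Abstract and the Discussion give 101 directly.
- Nine centres × 12 = 108. A target of 101 needs 101/9 = 11.2 per centre, which rounds up to 12. A target of 81 needs 81/9 = 9 per centre, which does not fit.

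**Step 4: take the design sentence literally.** 81 recruited × 0.80 = 64.8, about 65 pairs.

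**Step 5: power on the plan's own formula.** Power = Φ(D/SE − 1.645), with SE = √(2P(1 − P)/n).

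| Success rate | Pairs | SE | D/SE | Power |
|---|---|---|---|---|
| 95% | 81 | 0.0342 | 2.920 | 89.9% |
| 95% | 65 | 0.0382 | 2.616 | 83.4% |
| 97% | 65 | 0.0299 | 3.342 | 95.5% |

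At 97% success, 65 pairs also exceed the 49 that Table 2 asks for.

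**The case against.** **It is a wording slip that the document itself resolves.** The design sentence refers to the Sample size section, which is explicit, and the Abstract, Discussion and centre average all point to 101 or slightly more. This stands. It makes clear which sentence to change and makes an actual stop at 81 unlikely. It does not remove the contradiction, because the sentence still misstates an enrolment target.

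**The 20% might be meant as screening failure.** This does not stand. The Sample size section calls it dropout and bases it on earlier trials. If it were screening failure, the plan would have no allowance for two years of attrition.

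**Dropouts are not worthless.** The primary analysis is an intention-to-treat Cox model with shared frailty and visits every six months, so a child who leaves after a visit still contributes censored time. This stands in part. The power figures come from the plan's two-proportion formula for independent groups, and are indicative rather than exact for the planned analysis.

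**A reader might infer a much larger loss.** Judged by two one-sided tests at 95% success, power with 65 pairs is about 67%; judged by a 95% confidence interval it is about 49%. Most of the gap from 90% comes from changing the test. With the intended 81 pairs those figures are already about 80% and 66%. The choice of test is a separate matter and should not be charged to this sentence.

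**A reader might also infer that the trial necessarily misses its power, or that the centre average is a third conflicting target.** The documents support neither. At 97% success, within the planned range, power holds with 65 pairs, and 108 is consistent with 101 rounded up by centre.

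**Conclusion.** The point holds as an internal contradiction about the enrolment target. The design section's sentence is wrong by the plan's own arithmetic, and the Sample size section, Abstract and Discussion agree against it.

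The consequence is conditional. If recruitment stopped at 81 and 20% of children then contributed nothing, about 65 pairs would remain. Power at 95% success and a 10-point margin would fall from 90% to about 83%; at 97% success it would be about 95%. This rests on the plan's one-sided formula for independent groups and on its own dropout rate. Nothing in the documents instructs sites to stop at 81, so this is the effect of following the sentence literally, not a forecast. The sentence should be corrected because recruitment depends on the target and the correction costs nothing.

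**What to change.** In Trial design and blindness, replace the sentence with: *101 children will be enrolled and randomised so that, after about 20% dropout, about 81 pairs are evaluable; screening continues until that number is randomised.*

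Keep 101, the figure already used in the Abstract, Sample size section and Discussion. Strict rounding up of 101.25 would give 102, but the difference is trivial and does not justify a second number. The average of 12 per centre in Recruitment procedures can stay.

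The cost is one sentence of text. No child is added beyond those already planned, and neither the calculation nor the analysis changes.
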